#### Analysis of the primary outcome

To answer the primary outcome, functional independence assessed with the modified Rankin Scale (mRS) will be evaluated 90 days after the endovascular thrombectomy by trained research staff who are blinded to the randomization group. To enhance the follow-up rate, we have defined the assessment window as 90 ± 14 days after the procedure to account for factors such as holidays. The mRS is a 7-grade categorical scale ranging from 0 (no symptoms) to 6 (death). A dichotomous variable “efficacy” (success) will be created from the mRS scale, with success defined as an mRS of 0–2 indicating functional independence.

To determine the efficacy between the two clinical approaches, regression techniques will be employed, and the relative risk along with its 95% confidence (RR [IC 95%]) will be calculated. Univariate logistic regression models will be built for each independent variable. Selection of independent variables for inclusion in multivariate models will be based on clinical judgment and statistical considerations, including correlation with the dependent variable, and the coefficients and *p*-values obtained in the univariate models. Multivariate models with the selected independent variables candidates will be built using stepwise criteria, and the Akaike Information Criterion (AIC) will be calculated to identify the model that best explains the outcome.

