### Sample size {14}

We aim to compare neurological functional status at 90 days according to the modified Rankin scale (mRS), of patients with stroke who underwent endovascular thrombectomy with satisfactory results and who underwent early extubation (< 6 h) compared to delayed extubation (6–12 h). Efficacy will be assessed with the proportion of patients with functional independence (mRS scale ≤ 2).

A previous observational study [20] reported that 55.5% of patients achieved an mRS score of ≤ 2 after receiving early extubation (mechanical ventilation for less than 6 h), compared to 33.9% when extubation was delayed (mechanical ventilation for more than 6 h). In present trial, we hypothesize that early extubation, compared with delayed extubation, is associated with a better functional outcome 3 months after endovascular thrombectomy under general anesthesia for acute ischemic stroke. We have decided to set the level of significance at 5% (*α* = 0.05), with a power of 80% (*β* = 0.80), and to use a bilateral test (c = 2). We will work with two independent samples and both groups will be balanced (w1 = 0.5). Considering an expected percentage of losses is 5.00%, it would be necessary to include 87 individuals in each group, totaling 174 patients in the study. Depending on the course of the study, an interim analysis will be conducted when 70% of the recruited sample is reached, if deemed appropriate by the research team.We hypothesized that early compared with delayed extubation is associated with a better functional outcome 3 months after endovascular thrombectomy treatment under general anesthesia for acute ischemic stroke.

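### The primary efficacy analysis is described only as data-driven model building: no single treatment comparison is fixed, and the route to the promised relative risk is not stated

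*Protocol article*

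**What the plan says.** The protocol article, Statistical methods {20a}, Analysis of the primary outcome, dichotomises the 90-day mRS (success is 0–2). It says regression will be used to judge efficacy between the two approaches, and the effect measure is "the relative risk along with its 95% confidence" interval. The modelling steps that follow are:

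- "Univariate logistic regression models will be built for each independent variable".
- Variables for the multivariate models are chosen by clinical judgment and by statistical considerations: correlation with the outcome, and the coefficients and p-values of the univariate models.
- "Multivariate models with the selected independent variables candidates will be built using stepwise criteria", and AIC identifies the model that explains the outcome best.

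The section gives no other method for the primary comparison. Secondary outcomes have their own section with different wording. Sample size {14} rests on two independent proportions, two-sided at 5% with 80% power, and mentions no covariates. Section {20c} states intention to treat. The Secondary objectives include a search for factors linked to poorer functional status at discharge and at 90 days.

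**The concern.** Screening on univariate p-values followed by stepwise selection and AIC is a way to build a prognostic model. A randomised comparison needs something else: one contrast between arms, fixed in advance. As written, the endpoint, analysis population and effect measure are fixed, but the model that produces the estimate is not. Three things are left open:

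- whether treatment is kept in every model or competes with the other variables;
- whether candidates must precede randomisation;
- how a relative risk is derived when the only model named is logistic, whose direct output is an odds ratio.

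The choice of covariates matters even under randomisation, because an adjusted odds ratio is conditional on the covariates in the model. Changing the set changes the quantity estimated as well as its precision. At stake is whether the headline result can be traced to a decision made before the data were seen.

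**Working it through.** **1. What the trial was sized for.** Inputs from Sample size {14}: "55.5% of patients achieved an mRS score of ≤ 2 after receiving early extubation", "compared to 33.9% when extubation was delayed", two-sided α = 0.05, power 80%, equal groups, 5% losses.

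With p1 = 0.555, p2 = 0.339 and mean p̄ = 0.447, the pooled-variance formula is

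n = [1.960 × √(2p̄(1 − p̄)) + 0.842 × √(p1(1 − p1) + p2(1 − p2))]² / (p1 − p2)²

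- First root: √(2 × 0.447 × 0.553) = √0.4944 = 0.703
- Second root: √(0.2470 + 0.2241) = √0.4711 = 0.686
- n = (1.378 + 0.578)² / 0.216² = 3.825 / 0.04666 = 81.98, so 82 per arm
- With losses: 82 / 0.95 = 86.3, so 87 per arm and 174 in total

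This reproduces the 87 and 174 given in that section. The sizing is an unadjusted comparison of two proportions, which the analysis section never names as the primary analysis.

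**2. Relative risk against odds ratio at the same rates.**

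- RR = 0.555 / 0.339 = 1.64
- OR = (0.555 / 0.445) / (0.339 / 0.661) = 1.247 / 0.513 = 2.43
- Risk difference = 0.555 − 0.339 = 21.6 percentage points
- OR / RR = 2.43 / 1.64 = 1.48

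Success is common in both arms, so an odds ratio read as a relative risk would overstate it by about half.

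**3. Illustrative simulation of the selection.** These assumptions are not in the protocol: 166 evaluable patients, 10 baseline covariates of which 6 are prognostic, a univariate screen at p < 0.20, then stepwise AIC with treatment as one of the candidates.

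| Result | No effect (3,000 runs) | Conditional log-odds ratio 1.05 (1,500 runs) |
|---|---|---|
| Unadjusted, significant | 5.7% | 76% |
| Fixed adjusted model, significant | 5.0% | 81% |
| Free stepwise: treatment retained | 11% | 89% |
| Free stepwise: retained and significant | 4.7% | 81% |
| Smallest p-value of four analyses below 0.05 | 8.5% | 86% |

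The four analyses are unadjusted, fixed adjusted, stepwise with treatment forced in, and free stepwise. With a real effect, treatment was dropped in 100 − 89 = 11% of runs, which leaves no estimate. A second simulation, with 174 patients, no univariate screen, and 2 strong, 2 weak and 6 null covariates, dropped treatment in 4% of runs at an effect of about 21 points. The difference between 4% and 11% shows how far the figure depends on assumed covariate strengths.

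**The case against.** The best defence is that the paragraph merges two aims. The Secondary objectives include finding factors related to 90-day mRS, and univariate screening, stepwise building and AIC suit that aim. On this reading a crude relative risk is the headline and the stepwise models are exploratory. The reading is possible, but the section does not say so: it introduces the modelling as the way to determine efficacy, and the secondary outcomes are dealt with separately.

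A reader might also infer more than the protocol supports:

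- **That treatment is only a candidate and will be dropped.** This is inferred from silence. The text neither keeps treatment in nor says it may go.
- **That post-randomisation variables will be adjusted for.** Ventilation duration, ICU complications and day-1 and day-2 NIHSS appear in the list of data to be recorded, which is not a list of candidates. The subgroup variables in {20b} all precede randomisation. The text does not exclude later variables, and that is as far as the point goes.
- **That the result will be on the wrong scale.** The stated measure is the relative risk. Logistic regression is named only for the univariate models, and a relative risk can come from the 2×2 table, a log-link model or standardisation after logistic regression. Nothing says an odds ratio will be reported as a relative risk.
- **That selection is purely mechanical.** Clinical judgment is also a criterion, though an unspecified one leaves room for discretion.
- **That type I error is badly inflated.** One path followed once stayed near 5%. The 8.5% requires reporting the best of several analyses, which the protocol does not plan.

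A statistical analysis plan could supply the missing detail. Here, however, the protocol states a method, so a plan that follows it inherits the problem and one that departs from it contradicts the protocol.

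**Conclusion.** The point holds in this form: the only described route to the primary result is outcome-driven model selection, with no single treatment comparison named as primary and no stated derivation of the relative risk. The gap between RR 1.64 and OR 2.43 is exact arithmetic at the planning rates. It shows why the derivation must be stated, not that an error has been made. The simulated figures (treatment lost in roughly 4% to 11% of trials near the planning effect; 8.5% type I error if the best of four analyses is quoted) are illustrative and rest on covariate strengths that the protocol does not give. The harm is an unfixed, possibly lost, treatment estimate and freedom to choose among models.

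**What to change.** Reword Analysis of the primary outcome as follows:

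- Name one intention-to-treat comparison of mRS 0–2 as primary, with treatment always in the model and a short covariate list fixed in advance from baseline data already collected, for example age and NIHSS at admission.
- Report the relative risk with its 95% confidence interval from a log-link or modified Poisson model, or from logistic regression with marginal standardisation, and say which. Give the unadjusted relative risk and risk difference alongside.
- Allow no post-randomisation variable in the treatment-effect model.
- Move univariate screening, stepwise selection and AIC to the prognostic-factor objective and label them exploratory.

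The cost is one reworded section, submitted to the ethics committee as an amendment before database lock and preferably before the optional interim look at 70% of the sample. It needs no new data or patients, and the planned sample size is unchanged.

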#### Analysis of the secondary outcomes

The techniques that will be used to answer the secondary objectives will be fundamentally statistical inference techniques. The selection of each of them will depend on the nature of the variables involved, as well as their adjustment to normality.

All these analyses will be carried out with the statistical program SPSS 19.0 and those whose *p*-value is lower than 0.05 will be considered statistically significant values.

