#### Secondary objectives

The study will also investigate the effect of early (< 6 h) vs delayed (6–12 h) extubation after endovascular thrombectomy under general anesthesia for acute ischemic stroke, examining additional outcomes: the percentage of patients unable to be extubated in the assigned group, NIHSS scores on days 1 and 2, time to hospital discharge, mRS scores at hospital discharge, complications during ICU and hospital stay, and lengths of stay in the ICU and Hospital. We aim to identify factors that may influence poorer functional status at hospital discharge (NIHSS and mRS scores) and at 90 days (mRS score).

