#### Secondary outcomes measures

The secondary outcomes of this study will be as follows:NIHSS score at day 1, day 2, and at the time of hospital discharge.mRS at the time of hospital discharge.Percentage of patients who cannot be extubated in the assigned group.Complications associated with mechanical ventilation: pulmonary injuries (barotrauma or volutrauma), respiratory infections (ventilator-associated pneumonia, bronchoaspiration), airway, oral or pharyngeal injuries, and others.Complications during ICU and hospital stay: intracranial hemorrhage, hemorrhagic transformation, reperfusion syndrome, need for craniectomy, prolonged mechanical ventilation in ICU (> 24 h), prolonged mechanical ventilation in ICU (> 48 h), reintubation, prolonged ICU stay (> 48 h), pneumonia, bronchoaspiration, other infection, in-ICU mortality, in-hospital mortality, and other complications.ICU and Hospital length of stay.Work-flow time, including stroke onset to door time, to artery puncture, and to reperfusion or procedure completion.

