## Assignment of interventions: allocation

### Sequence generation {16a}, concealment mechanism {16b}, implementation {16c}

Randomization will be performed immediately after the patient is admitted to the ICU. Enrolled participants will be randomized in a 1:1 ratio for early or delayed extubation. To ensure balance between the two groups, a computer-generated random block number table will be used (blocks of 8). A designated staff member, not involved in extubation, anesthesia management, or follow-up will handle recruitment and generate the allocation randomization sequence. The staff member will implement the allocation sequence through opaque, sealed, and stapled envelopes.

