## Statistical methods

### Statistical methods for primary and secondary outcomes {20a}

#### Description of the patient groups at baseline

The baseline characteristics of all patients will be described. Categorical variables will be reported as absolute numbers (*n*) and percentages and quantitative variables as either means (standard deviation) or medians (25th percentile–75th percentile). Data will be analyzed using chi-square and Wilcoxon rank-sum test (or paired samples *T* test) as appropriate. Pearson or Spearman correlation coefficient will be calculated to compare patient specifics between groups at the baseline. Normality will be calculated with Kolmogorov–Smirnov test with Lilliefors correction.

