### Methods for additional analyses (e.g., subgroup analyses) {20b}

Primary outcome will be analyzed in following subgroups: age, gender, body mass index, NIHSS score at admission, ASPECTS, site of arterial occlusion, time from symptom onset to endovascular thrombectomy, use of intravenous thrombolysis.

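### Follow-up NIHSS is left to a normality-driven choice of technique; one comparison adjusted for the admission NIHSS already collected should be prespecified instead

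*Protocol article*

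**What the plan says.** The first-listed secondary outcome in the protocol article (Secondary outcomes measures) is "NIHSS score at day 1, day 2, and at the time of hospital discharge". The same scale is scored at arrival (Table 1) and is recorded as a baseline variable (Data collection and management).

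On method, Analysis of the secondary outcomes says "The techniques that will be used to answer the secondary objectives will be fundamentally statistical inference techniques", and then "The selection of each of them will depend on the nature of the variables involved, as well as their adjustment to normality". It adds a 0.05 significance threshold and the software, and names no test, model or covariate.

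Four other places bear on the point:

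- **Description of the patient groups at baseline** names two-group tests, "Data will be analyzed using chi-square and Wilcoxon rank-sum test (or paired samples" t test), and a Kolmogorov–Smirnov check of normality with Lilliefors correction.
- **Analysis of the primary outcome** is the only place that describes regression and covariate selection.
- **Methods for additional analyses** gives admission NIHSS a role, but for the primary outcome only: "Primary outcome will be analyzed in following subgroups: age, gender, body mass index, NIHSS score at admission".
- **Sequence generation** describes blocking, "a computer-generated random block number table will be used (blocks of 8"), and mentions no stratification.

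**The concern.** A rule that looks only at variable type and normality has two consequences for a scale measured before and after randomisation.

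First, the test, and with it the quantity compared (a mean difference or a shift in ranks), depends on a check of the trial's own data. The three time points could end up with different tests.

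Second, the rule gives the admission value of the same scale no part in the comparison. Admission severity can vary widely, since entry requires NIHSS of at least 6 with no stated upper limit on a scale of 0 to 42. The article itself lists NIHSS among the factors that may influence outcome (Background and rationale; Discussion). Neither the allocation as described nor the analysis as described takes it into account here.

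At stake is precision on the first-listed secondary outcome, and protection against a chance difference in admission severity being taken for an effect of extubation timing.

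**Working it through.** **1. The plan's own figure.** No figure is given for NIHSS; the only sample size is for mRS 0–2 at 90 days. Inputs (Sample size): 55.5% and 33.9%, two-sided 5%, 80% power, 1:1 allocation, 5% losses. With pooled variance and mean proportion 0.447:

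n = [1.960·√(2·0.447·0.553) + 0.842·√(0.555·0.445 + 0.339·0.661)]² / 0.216² ≈ 82 per arm

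82/0.95 = 86.3, so 87 per arm and 174 in total. The stated 174 is reproduced. It gives 82 evaluable per arm for the steps below.

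**2. Gain from adjustment.** Let ρ be the correlation between admission and follow-up NIHSS. Adjustment multiplies the variance of the arm difference by 1 − ρ². For an effect with 80% power unadjusted:

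power = Φ[(1.960 + 0.842)/√(1 − ρ²) − 1.960]

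The last column is 174/(1 − ρ²), the unadjusted total that would match 174 adjusted. Neither ρ nor the 80% starting power for NIHSS is in the document; both are assumptions.

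| ρ (assumed) | 1 − ρ² | Power after adjustment | Matching unadjusted total |
|---|---|---|---|
| 0.3 | 0.91 | 83.6% | 191 |
| 0.4 | 0.84 | 86.4% | 207 |
| 0.5 | 0.75 | 89.9% | 232 |
| 0.6 | 0.64 | 93.8% | 272 |
| 0.7 | 0.51 | 97.5% | 341 |

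The gain reaches 5 percentage points at ρ of about 0.36.

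**3. Does this carry over to skewed scores and ranks?** A simulation used 4,000 trials per scenario, 82 per arm, skewed NIHSS-like scores and a latent correlation of 0.5. Power was 79.4% for the Wilcoxon test and 88.0% for rank-based ANCOVA. Rejection under the null was 4.9% and 5.1%. The gain is close to the formula's, and both tests hold their level.

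**4. Chance imbalance.** In 1 trial in 20 the arms differ in mean admission NIHSS by more than 1.96·SD·√(2/82) = 0.306 SD. For an assumed SD of 5, 6 or 7 points that is 1.53, 1.84 or 2.14 points.

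An imbalance of exactly that size carries ρ·0.306 SD into the unadjusted follow-up difference: 0.09, 0.15 and 0.21 SD at ρ = 0.3, 0.5 and 0.7. Given that imbalance, the type I error of the unadjusted test is

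1 − Φ[1.96(1 − ρ)/√(1 − ρ²)] + Φ[−1.96(1 + ρ)/√(1 − ρ²)]

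which is 7.9%, 12.9% and 20.5%. Averaged over all randomisations it is 5%.

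**The case against.** A reader might infer that the plan commits to an unadjusted two-group test for NIHSS. The text does not support that. The secondary-outcome section names no test and does not exclude a covariate; the Wilcoxon and t tests appear only under the baseline description. The secondary objectives also include "We aim to identify factors that may influence poorer functional status at hospital discharge (NIHSS and mRS scores"), so relating baseline factors to discharge NIHSS is within scope. That objective gives no method, however, and does not promise an adjusted comparison between arms.

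A reader might also infer that leaving out baseline NIHSS biases the result. It does not. Over randomisations the unadjusted comparison is unbiased with a 5% type I error. The article's remarks on NIHSS as an influence are made mainly in criticism of observational studies, and randomisation deals with that kind of confounding.

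The strongest objection is that covariates for a secondary outcome are commonly left to a statistical analysis plan, which is not shown. A missing covariate would indeed not be a point by itself. But this section is not silent: it sets a selection rule for every secondary outcome and does not refer to a later document. The objection limits how firmly the result of that rule can be stated; it does not make the rule a good one.

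Finally, the size is uncertain. Admission NIHSS precedes thrombectomy, and only patients with NIHSS of at least 6 and successful reperfusion are eligible. Both can weaken the correlation with later scores. At ρ = 0.3 the gain is only 3.6 percentage points. This stands.

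**Conclusion.** The point holds as a matter of efficiency and prespecification. The only stated rule for follow-up NIHSS is a choice by variable type and normality. Its natural result is an unadjusted comparison, by inference from three sections of the article and not by its express words.

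That comparison would be valid but less precise than the available alternative, by a variance factor of 1 − ρ². The power gain from an assumed 80% is about 4 points at ρ = 0.3 and 10 points at ρ = 0.5. The second is what about 33% more patients would give (1/0.75 = 1.33). Exposure to chance imbalance is real in an individual trial but is not a systematic error. The correlation, the NIHSS standard deviation and the starting power are all assumptions.

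The point concerns a secondary outcome and is worth correcting. It does not touch the primary analysis, the sample size of 174 or the validity of the trial.

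**What to change.** In Analysis of the secondary outcomes, replace the normality-driven choice for NIHSS with one named method, along these lines:

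> NIHSS at day 1, day 2 and hospital discharge will each be compared between randomised groups by rank-based analysis of covariance: the ranked follow-up score is regressed on group and ranked admission NIHSS. The unadjusted Wilcoxon rank-sum test will be reported as a sensitivity analysis, whatever the distribution of the scores.

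Another model adjusted for admission NIHSS would serve as well, provided that one is chosen before the outcome data are compared by arm. If a statistical analysis plan already fixes such a model, a reference to it is enough.

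How deaths before an NIHSS assessment are handled is a separate choice of estimand and not part of this change.

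The cost is one or two sentences. Admission NIHSS is already collected, so no new data, visits or patients are needed, and the model can be run in the software already named. The article reports 70 patients randomised by February 2024 and recruitment continuing to about September 2026, so by its own timetable the change can be made before the final analysis.

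### The article labels every secondary result with p below 0.05 statistically significant, across about 26 partly overlapping components, with no multiplicity control or exploratory label

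*Protocol article*

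**What the plan says.** The rule is in the protocol article under Analysis of the secondary outcomes. That section first leaves the choice of test open: "The selection of each of them will depend on the nature of the variables involved, as well as their adjustment to normality". It then ends by naming the software, "All these analyses will be carried out with the statistical program SPSS 19.0", and in the same sentence says that results with a p-value "lower than 0.05 will be considered statistically significant values".

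The outcomes it governs are listed under Secondary outcomes measures. They include "NIHSS score at day 1, day 2, and at the time of hospital discharge", "mRS at the time of hospital discharge", "Percentage of patients who cannot be extubated in the assigned group", a group of ventilation complications, a longer group that begins "Complications during ICU and hospital stay: intracranial hemorrhage, hemorrhagic transformation, reperfusion syndrome, need for craniectomy", two lengths of stay, and work-flow times.

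The article names one primary outcome, mRS 0–2 at 90 days, and the Sample size section attaches a two-sided 5% level to it. No hierarchy, adjustment or exploratory label for the secondary outcomes appears anywhere in the article.

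**The concern.** A 5% threshold limits the error of one test. Applied separately to each item on a long list, it does not limit the chance that something on the list crosses the line when nothing is going on. Because the article fixes the label in advance, an author who follows it must call each such result statistically significant, whether it is the only one or one of several.

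The secondary list holds pneumonia, reintubation, intracranial hemorrhage, mortality and length of stay. Readers will look to these when weighing early against delayed extubation, and the Discussion hopes the data will support a recommendation on timing. A chance finding among them, reported with the same label as the primary result, could be given weight it has not earned.

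**Working it through.** **The plan's own figures.** The article states no familywise error rate. Its only error figure for secondary outcomes is 0.05 per test. Its sample size, used below for the rare-event check, reproduces. The inputs are 55.5% versus 33.9%, two-sided 5%, 80% power, 1:1 allocation and 5% losses (Sample size section). With pooled variance under the null and mean rate 0.447:

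n = [1.960 × √(2 × 0.447 × 0.553) + 0.842 × √(0.555 × 0.445 + 0.339 × 0.661)]² / 0.216² ≈ 82 per group

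82 / 0.95 = 86.3, rounded up to 87 per group and 174 in total, as stated.

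**Counting the components** (Secondary outcomes measures):

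| Group | Components |
|---|---|
| NIHSS at day 1, day 2 and discharge | 3 |
| mRS at discharge | 1 |
| Not extubated as assigned | 1 |
| Ventilation complications (pulmonary injury, ventilator-associated pneumonia, bronchoaspiration, airway/oral/pharyngeal injury, others) | 5 |
| ICU and hospital complications | 14 |
| ICU and hospital length of stay | 2 |
| **Total** | **26** |

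The three work-flow times are left out because they are fixed before randomization; including them gives 29. Six of the 26 are scales or durations (3 + 1 + 2) and 20 are binary (1 + 5 + 14).

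**Reference case: no true effects, independent tests, each of exact 5% size.**

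- Chance of at least one false positive: 1 − 0.95^26 = 0.736.
- Expected number: 26 × 0.05 = 1.3.

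**Correlated outcomes.** The article gives no correlations, so these are assumptions: equal correlation among 26 normal test statistics, 200,000 simulated trials, each test still of 5% size.

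| Assumed correlation | Chance of at least one |
|---|---|
| 0.2 | 67.5% |
| 0.3 | 61.8% |
| 0.5 | 47.5% |
| 0.7 | 32.4% |
| 0.8 | 24.5% |

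Correlation alone leaves the expected count at 1.3.

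**Rare events.** Tests of rare binary events often have a true size below 5%. The event rates are again assumptions, common to all 20 binary outcomes, with 87 per group and independent tests. The formula is 1 − 0.95^6 × (1 − s)^20, where s is the exact size of the binary test.

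| Assumed event rate | s, chi-square | Chance | s, Fisher | Chance |
|---|---|---|---|---|
| 1% | 0.0096 | 39.4% | 0.0002 | 26.8% |
| 2% | 0.0347 | 63.7% | 0.0030 | 30.8% |
| 5% | 0.0420 | 68.8% | 0.0180 | 48.9% |
| 10% | 0.0502 | 73.8% | 0.0299 | 59.9% |
| 20% | 0.0494 | 73.3% | 0.0316 | 61.3% |

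Here the expected count falls too. With Fisher tests at a 1% event rate it is 6 × 0.05 + 20 × 0.0002 ≈ 0.30.

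Correlation and rarity were examined separately. Together they would lower the figure further.

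**The case against.** The strongest reply is that 74% describes a situation the list does not match. Ventilation beyond 48 h is nested in ventilation beyond 24 h, ICU stay beyond 48 h is a cut of ICU length of stay, and in-ICU deaths are a subset of in-hospital deaths. Bronchoaspiration is listed twice, NIHSS is measured three times in the same patients, and two items are catch-alls. Some events may be rare. The arms may also truly differ in how often the assigned window is met, so a significant result there need not be false. All of this stands. A reader might infer that at least one false claim is likely, but the article supplies no correlations or event rates that would establish it, and under several assumptions the chance is below one half.

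A reader might also infer that the rule covers the eight factors in the section on additional analyses, which says "Primary outcome will be analyzed in following subgroups". The text does not support this. The rule closes the section on secondary outcomes. The subgroups come later, under their own heading, concern the primary outcome, and have no stated p-value threshold.

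A third reply is that multiplicity is commonly left to a statistical analysis plan, and that significance at 0.05 can be read as a nominal label. That would answer a complaint about silence. Here the article itself states the rule, without the word nominal, and a later plan that restricted these claims would have to depart from it.

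Finally, the Discussion does not tie its hoped-for recommendation to secondary p-values. That is correct, and it limits the consequence to a risk of over-reading.

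**Conclusion.** The point holds in a limited form. The article fixes an unadjusted 0.05 significance label for about 26 partly overlapping secondary components and does not mark any of them as exploratory. With no true effects, the familywise error is about 74% under independence and exact 5% test size. It ranged from about 24% to 74% across the correlations and event rates tried, all of which are assumptions. Every figure is several times 5%, so the conclusion does not depend on the choice among them. The primary outcome's 5% level is untouched. What is at risk is the reading of the secondary results.

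**What to change.** Replace the closing rule under Analysis of the secondary outcomes with text such as: *Only the comparison of functional independence (mRS 0–2) at 90 days will be tested for a claim, at the two-sided 5% level. Secondary outcomes will be reported as effect estimates with 95% confidence intervals and labelled exploratory; any p-values shown are nominal.*

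This needs no further patients or data and touches no aspect of care. Recruitment was still open when the article was written, so the wording can be settled before the final analysis. The cost is that no secondary result can be claimed as confirmed. Formal adjustment would be the alternative, but Bonferroni over 26 components means 0.05 / 26 = 0.0019 per test, a demanding threshold for a trial sized on its primary outcome alone.
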